### Hypotheses

To evaluate the impact of these three different implementation strategies for IBSM in current clinical practice, we have proposed four hypotheses, which are constructed to compare the effect of tailoring implementation strategies to identified barriers (IS and ES) versus a commonly used, non-tailored strategy (MS):

1. More general practices will participate in IBSM in the IS or ES strategy as compared with the MS strategy;

2. The proportion of referred patients who participate in the IBSM program in the ES or IS strategy will be greater as compared with the MS strategy;

3. The proportion of referred patients who participate in the IBSM program in the ES or IS strategy will be greater as compared to the MS strategy;

4. The ES and the IS strategy will be more cost-effective as compared to the MS strategy.

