## Methods

### Study design

This study is a three-arm, cluster randomized trial with a cluster pre-randomisation design
[7] (Figure 
1). Because the implementation strategies are primarily targeted at general practices, randomisation will occur at practice level (CONSORT guidelines for cluster trials, Table 
1[27]). Prior to obtaining informed consent from GPs and patients, practices will be allocated to one of the strategies. Follow-up per practice is 12 months. At patient level, follow-up duration is six months. In the ES and IS strategies, individual patient outcomes will be evaluated at baseline (first visit of a patient to the general practice for instruction on IBSM), and three and six months after a patient’s start with IBSM. Individual patient outcomes in the MS strategy will be evaluated at six months (end-point evaluation) after a patient’s start with IBSM.

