**Quality of life/patient utilities**			
Asthma related quality of life (AQLQ)	A	A	A,N
Utilities: (EQ-5D)	X	X	A,N

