**Costs**			
Healthcare and other costs (CostQ)	X	X	X, N

A = all strategies; X = Intermediate and Extended strategy; N = non-participating practices.

Asthma control is using the 7-item Asthma Control Questionnaire (ACQ), the optimal cut-point for ‘controlled’ is ≤0.75 and a value of ≥1.50 confirms ‘not controlled’ asthma
[28]. Lung function will be measured as the Forced Expiratory Volume in one second (FEV_1_). Patients receive a handheld electronic spirometer (PiKo-1: Ferraris; Hertford, UK) and are instructed to report the highest value of three measurements in the morning before taking medication
[1]. The presence of exacerbations is assessed; they are defined as deterioration in asthma that required emergency treatment or hospitalization (collected by quarterly questionnaire) or the need for oral steroids for three days or more (collected by pharmacy records) or the need for oral steroids for asthma as judged by the attending physician.

Exacerbations are defined according to ATS/ERS statement
[40]:

Severe exacerbations require at least one of the following: systemic corticosteroids (tablets, suspension, or injection) usage or an increase from a stable maintenance dose, for three or more days; or a hospitalization or emergency room visit because requiring systemic corticosteroids.

Moderate exacerbations require ≥ 1 of the following features, lasting for two or more days: deterioration in symptoms, deterioration in lung function, and/or increased rescue bronchodilator use.”

Health education impact is assessed by the health education impact questionnaire (heiQ)
[41]. Self-reported medication adherence is measured by the Medication Adherence Report Scale
[32]. Illness perceptions are assessed by using the Brief Illness Perception Questionnaire (Brief IPQ)
[33]. In addition, asthma symptom utilities are obtained from the Asthma Quality of Life Questionaire (AQLQ)
[42], EQ-5D
[31,43] and a visual analogue scale (VAS).

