#### Economic evaluation

The economic evaluation includes outcomes on cost-effectiveness and cost-utility. Medical costs, such as prescribed medication are assessed from electronic patient records (with written patient permission) complemented with the patient’s report on medication purchased elsewhere
[44]. In addition, actual treatment advice by the care provider and treatment advice by the system are registered. Healthcare consumption, absenteeism and productivity loss, and the number of limited activity days are measured by using the Cost Questionnaire
[34]. Furthermore, data on patient contacts (frequency of in-practice routine asthma consultations, telephone/email consultations, and unscheduled visits) are registered.

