#### Economic evaluation

The economic evaluation compares differences in societal costs to differences in the number of limited activity days (CEA) and quality-adjusted life years (CUA). The analysis has a six-month time horizon, without discounting. Group averages are statistically compared using two-sided bootstrapping and net-benefit analyses are used to compare costs to patient outcome. Sensitivity analyses are performed on the perspective (societal versus healthcare perspective) and the applied utility measure (Dutch EQ5D, VAS).

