#### Cost-effectiveness

Cost-effectiveness of treatment strategies is evaluated by incremental net-benefit analysis
[46]. Net health benefit addresses cost-effectiveness ratios by assuming values for the willingness to pay per unit of effectiveness. The cost analysis includes both medical (medication, visits, and hospitalizations) and non-medical costs (productivity losses, informal care). Other costs are estimated using quarterly cost questionnaires
[34] Costs are valued according to standard prices charges
[47] including time and travel costs.

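### Table 4 does not give the minimum-strategy arm the Cost Questionnaire or enough EQ-5D measurements for the planned societal cost-effectiveness comparison

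*Protocol article*

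**What the plan says.** All references are to the protocol article.

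- **Hypotheses.** The fourth hypothesis is "The ES and the IS strategy will be more cost-effective as compared to the MS strategy". MS is the comparator.
- **Economic evaluation (analysis).** The evaluation "compares differences in societal costs to differences in the number of limited activity days (CEA) and quality-adjusted life years (CUA", over six months. The societal perspective is the main one, and the healthcare perspective is a sensitivity analysis.
- **Economic evaluation (measurements).** Use of care, sick leave, lost productivity and "the number of limited activity days are measured by using the Cost Questionnaire". Medication costs come from patient records, and contacts with the practice are registered. Neither is limited to particular arms.
- **Analysis of clinical data.** Base-case QALYs use the Dutch EQ-5D tariff.
- **Table 4.** The legend reads "A = all strategies; X = Intermediate and Extended strategy; N = non-participating practices". The Cost Questionnaire row is X, X and X, N at 0, 3 and 6 months. The EQ-5D row is X, X and A,N. The Asthma Quality of Life Questionnaire (AQLQ) row is A, A and A,N.
- **Study design.** "Individual patient outcomes in the MS strategy will be evaluated at six months (end-point evaluation", which the Endpoint evaluation section repeats.
- **Cost-effectiveness.** "The cost analysis includes both medical (medication, visits, and hospitalizations) and non-medical costs (productivity losses, informal care". The Discussion adds that the costs of implementation are evaluated from a societal perspective.

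**The concern.** A cost-effectiveness comparison needs costs and effects measured in every arm compared. By its own legend, Table 4 gives the Cost Questionnaire to IS, ES and non-participating practices, but not to patients who take part under MS. Limited activity days are the effect measure of the cost-effectiveness analysis, and lost productivity is part of societal cost. Both come from that questionnaire. The cost-utility analysis has a related difficulty, because its base-case utility is measured once in MS and three times in the other arms.

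At stake is one of the four hypotheses and a stated objective of the trial. Patient-reported costs and utilities that were not collected cannot be recovered at the analysis stage.

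**Working it through.** The article gives no computed figure for the economic evaluation. The stated sample size concerns participation and does not bear on this point. The check is therefore a reading of Table 4 by arm, followed by the weights of a six-month QALY.

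**Step 1. Table 4 by arm**

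| Instrument | IS and ES | MS |
|---|---|---|
| Cost Questionnaire | 0, 3, 6 months (3 of 3) | none (0 of 3) |
| EQ-5D | 0, 3, 6 months (3 of 3) | 6 months (1 of 3) |
| AQLQ | 0, 3, 6 months | 0, 3, 6 months by Table 4; 6 months only by Study design |

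All three Cost Questionnaire cells are filled, so a shifted column does not explain the missing A. The table does use A where MS is meant, as in the six-month EQ-5D cell.

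**Step 2. What the analysis needs in MS, and its source**

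- Limited activity days: Cost Questionnaire, so no scheduled source.
- Sick leave and lost productivity: Cost Questionnaire, so no scheduled source.
- Prescribed medication: patient records, available.
- Practice consultations, telephone and email contacts, unscheduled visits: registered, available.
- Base-case utility: EQ-5D, six months only.

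**Step 3. Weight of the unmeasured times in a QALY**

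The article does not state how QALYs are integrated over time. The trapezoid rule is assumed here, with u0, u3 and u6 the utilities at 0, 3 and 6 months:

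QALY = 0.25 × (u0 + u3)/2 + 0.25 × (u3 + u6)/2 = 0.125 u0 + 0.25 u3 + 0.125 u6.

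The weights sum to 0.5 years. In MS only u6 is measured, so the unmeasured share is (0.125 + 0.25)/0.5 = 75%.

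**Step 4. Illustration with assumed utilities (none are in the article)**

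Take u6 = 0.85 and let u0 = u3 = u lie anywhere from 0.75 to 0.90:

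- u = 0.75: 0.375 × 0.75 + 0.125 × 0.85 = 0.3875
- u = 0.90: 0.375 × 0.90 + 0.125 × 0.85 = 0.44375

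The same six-month value is compatible with MS QALYs that differ by 0.44375 − 0.3875 = 0.05625. This shows only how little u6 alone fixes the QALY. It does not predict a bias.

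**The case against.** **The Table 4 entry may be a coding slip.** Giving the questionnaire to non-participating practices but not to MS participants makes little sense as a design. The Cost-effectiveness section also speaks of quarterly cost questionnaires without limiting them to any arm. This is plausible, but the schedule as printed is what sites would follow. A quarterly questionnaire would also conflict with the six-month-only evaluation of MS. The texts need reconciling whichever was intended.

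**Other MS data exist.** Medication records and registered contacts cover MS, so a reader who infers that there are no MS cost data, or that hypothesis 4 cannot be tested at all, goes too far. This part of the objection stands. However, these sources support only part of a healthcare-perspective comparison, and they supply no limited activity days.

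**The AQLQ is another utility source.** Table 4 codes it A at all three times, and asthma symptom utilities are derived from it. It is therefore not correct that MS has a single utility value of any kind. But the base case is the EQ-5D, the named sensitivity measure is a visual analogue scale, and the Study design section contradicts the AQLQ entries for MS at 0 and 3 months.

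**Sparse measurement in MS is deliberate.** The Discussion says research activity in MS is minimised because it could itself act as a stimulus. This stands, and it argues against adding a baseline or three-month contact in MS. It does not argue against one more instrument at the planned endpoint evaluation.

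**Delivery costs.** A reader might infer from the cost list that training, coaching and outreach costs are excluded, that the six-month horizon drops start-up costs, and that results will favour the more intensive strategies. The article does not support this. The Discussion says implementation costs are evaluated. Training attendance and providers' time in the system are recorded. A six-month horizon does not stop one-off costs being allocated to patients. Delivery costs are not itemised, which a condensed article may leave to the full protocol.

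**Conclusion.** The point holds in a limited form. Under Table 4 as printed, the societal cost-effectiveness and cost-utility analyses of IS and ES against MS cannot be carried out as specified. Participating MS patients have no scheduled source for limited activity days or lost productivity (0 of 3 time points). Their EQ-5D is measured at 1 of 3 time points, which leaves 75% of the weight of a trapezoid QALY on unmeasured times.

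The first result rests only on the printed table and the measurement section. The 75% also assumes the trapezoid rule. The size of any resulting error in QALYs or euros cannot be derived from the article, because it gives no utilities, threshold or unit costs for the strategies.

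The lack of itemised delivery costs is secondary. It is a matter of aligning two sections, not evidence of an exclusion.

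**What to change.** 1. **Table 4, Cost Questionnaire, six months:** change X, N to A,N. Collect it in MS at the existing endpoint evaluation, with recall covering the full six months.
2. **QALY method:** state one that treats all arms alike given the endpoint-only EQ-5D in MS, for example a comparison of six-month utilities in all arms. Otherwise narrow hypothesis 4 and the Economic evaluation section to what the MS data can support.
3. **MS schedule:** reconcile the A codes for the AQLQ at 0 and 3 months with the Study design and Endpoint evaluation sections, which give MS only a six-month evaluation.
4. **Secondary:** align the cost list in the Cost-effectiveness section with the Discussion by naming the costs of delivering the strategies, including those that arise in the start-up phase.

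The cost is one more questionnaire at a contact already planned, so no additional MS contact is needed. Two limits remain. MS patients would recall six months at once while IS and ES patients also report at three months, and a six-month utility comparison is a narrower result than a QALY. The CONSORT table says patient recruitment is ongoing, so the change can still reach MS patients who have not yet had their endpoint evaluation.

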#### Endpoint evaluation

Patients in practices randomized to the MS strategy, and those patients in the IS and ES strategy not willing to participate in IBSM support, will only be approached for an endpoint evaluation at six months after their start with PatientCoach.

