### Minimum strategy (MS)

#### Start-up phase basic components

Practice recruitment: practices receive an information letter on IBSM support by using PatientCoach. Practices will receive a reminder letter within four weeks.

Participating physicians will be asked whether their non-responding colleagues in their practices would be interested in participation. On meetings for professional groups and patient organisations PatientCoach team members will present information on self-management and web-based support.

Patient recruitment: GPs are asked to invite at least ten patients to use PatientCoach.

PatientCoach information session for participating practices: In addition to a general announcement, professionals receive a manual on PatientCoach. Professionals (GP and/or PN) have the opportunity to join a PatientCoach information session. This information session is focused on the principles and usage of the IBSM program by the PN and patients, including home measurement of lung function as forced expiratory volume in one second (FEV_1_) using an electronic hand-held spirometer (PiKo-1: Ferraris; Hertford, UK). Finally, a short on-site training in usage of the PatientCoach system focusing on integration within the local primary care information system is offered to practices.

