**Clinical**			
Asthma control (ACQ)	A	A,N	
Lung function (FEV_1_) []	A	A	A

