#### Analysis

The analysis is carried out on an intention-to-treat basis*.* Analyses include descriptive statistics and comparisons on process and effect evaluation. Differences are compared between implementation strategies using a random-effects analysis accounting for within-patient repeated measurements and clustering on general practice, or nonparametric comparisons, such as chi-square, as appropriate. All data are analyzed using STATA.

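### FEV1 is not scheduled for practices that were randomised but did not participate, so the between-strategy lung-function comparison cannot be the intention-to-treat comparison that the protocol states

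*Protocol article*

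**What the plan says.** The Abstract lists lung function among the secondary clinical outcomes. The Analysis section states "The analysis is carried out on an intention-to-treat basis" and compares outcomes between implementation strategies.

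The measurement schedule is Table 4. Its FEV1 row reads "Lung function (FEV_1_) [] A A A", and the quality-of-life row reads "Asthma related quality of life (AQLQ) A A A,N". The legend is "A = all strategies; X = Intermediate and Extended strategy; N = non-participating practices".

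On the source of FEV1, the text under Table 4 says "Patients receive a handheld electronic spirometer (PiKo-1: Ferraris; Hertford, UK) and are instructed to report the highest value of three measurements". The Minimum strategy start-up section describes an information session on "usage of the IBSM program by the PN and patients, including home measurement of lung function as forced expiratory volume in one second". Table 1 (Interventions) lists lung-function self-monitoring as a PatientCoach module, and the PatientCoach section lists home lung-function reminders as one of its tools.

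On who is followed, the section Blinding and strategy allocation randomises practices before consent and then sends each a letter describing its allocated strategy. The section Endpoint evaluation applies one rule to Minimum-strategy patients and to the unwilling in the other two arms: "those patients in the IS and ES strategy not willing to participate in IBSM support, will only be approached for an endpoint evaluation". That evaluation falls at month 6. The Study design section likewise places Minimum-strategy patient outcomes at six months only.

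**The concern.** An intention-to-treat comparison of strategies needs outcome data, or at least scheduled outcome data, from what was randomised. Here that is the practice, randomised before it decides whether to take part. For FEV1 the schedule stops at practices that joined. They join after learning their strategy, and hypotheses 1 and 2 predict that practice and patient participation will be higher under the Intermediate (IS) and Extended (ES) strategies than under the Minimum strategy (MS).

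If MS draws in a small, keen group and IS or ES a broader one, mean FEV1 can differ between strategies with no effect on lung function at all. The result would still be presented as an intention-to-treat effect. A later analysis plan cannot repair this, because the missing measurements were never scheduled.

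**Working it through.** **1. Table 4, row by row (6-month/end-point column)**

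| Outcome | End-point code | N present? |
|---|---|---|
| FEV1 | A | no, at any time |
| AQLQ | A,N | yes |
| EQ-5D | A,N | yes |
| heiQ | X,N | yes |
| Cost questionnaire | X,N | yes |
| MARS | X | no, at any time |
| B-IPQ | X | no, at any time |

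The ACQ row shows N under 3 months and an empty end-point cell. This may be a column shift from text extraction, so I do not rely on it. The authors extended several outcomes to non-participating practices, but not FEV1.

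**2. Is participation post-randomisation and expected to differ?** Yes on both counts. Allocation precedes consent, the invitation letter describes the allocated strategy, and hypothesis 1 states that more practices will take part under IS or ES. Invitation continues until enough practices per strategy participate, so practices that decline remain part of what was randomised.

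**3. Unwilling patients in participating practices.** Table 4 has no code for them. Three places (Table 1, the PatientCoach section, the Minimum strategy section) tie home FEV1 to the programme, so it is likely that they have none. The statement that patients receive a spirometer is unqualified, however, and the content of their six-month evaluation is not listed. This is an inference.

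**4. Baseline.** Table 4 gives FEV1 code A (all strategies) at 0 and 3 months. Study design and Endpoint evaluation give MS patients six months only. Both cannot be right. If the text governs, MS has no baseline FEV1 with which to compute change or adjust for selection.

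**5. Can the plan's rates size the selection?** First, the plan's own figure. With 5% against 30%, two-sided alpha 0.05 and power 0.80:

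- n = [1.96·√(2·0.175·0.825) + 0.842·√(0.05·0.95 + 0.30·0.70)]² / 0.25² = 35.1
- with continuity correction: (35.1/4)·[1 + √(1 + 4/(35.1·0.25))]² = 42.7, so 43
- design effect: 1 + (10 − 1)·0.25 = 3.25
- 43 × 3.25 = 139.75, i.e. 140 per arm and 420 in total, as stated.

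So the planned increase of 25% is consistent with percentage points, 5% to 30%. But the 5% is described as patients who frequently monitor, and usage is defined as ACQ monitoring in two of three months. A patient can enrol, hold a spirometer and report FEV1 without meeting that criterion. No enrolment or practice-participation rate is given.

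**6. Illustration (assumed, not from the documents).** Suppose the most willing fraction p supplies FEV1, willingness is normal and correlates ρ with FEV1 change, and no strategy has any effect. The mean among those measured is then ρ·φ(z)/p in SD units, where z is the upper-p point of the normal distribution.

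- p = 5% against 30%: ρ·(2.063 − 1.159) = 0.904ρ, or 0.09 to 0.27 SD for ρ = 0.1 to 0.3
- p = 20% against 60%: ρ·(0.280/0.20 − 0.386/0.60) = ρ·(1.400 − 0.644) = 0.756ρ, or 0.08 to 0.23 SD
- equal p: zero.

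The spurious difference favours MS if ρ is positive and IS/ES if it is negative. This shows the mechanism only. Neither p nor ρ is known.

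**The case against.** The strongest case against has four parts.

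- **The legend.** N stands for non-participating practices, not patients, and A means all strategies. FEV1 has code A in the column headed 6 months / end-point, so unwilling patients in participating practices might be measured then. This stands. A reader might infer that FEV1 is never measured in anyone who declines the programme; the documents make that likely but do not state it. The gap at practice level is unaffected.
- **The rates.** A reader might also infer a sixfold difference in who supplies FEV1: 140 × 0.05 = 7 MS patients against 140 × 0.30 = 42 in IS or ES, with a standard error of √(1/7 + 1/42) = 0.41 SD instead of √(2/140) = 0.12 SD. The documents do not support this. Those rates describe frequent monitoring, not enrolment or spirometer holding.
- **Scope.** Lung function is one of several secondary outcomes, the primary outcomes and sample size are untouched by this point, and a condensed article may leave analysis sets to the analysis plan. All fair, and it limits the severity. But the measurement schedule and the intention-to-treat label are both fixed in this article and conflict for FEV1.
- **The remedy.** Non-participating practices have AQLQ at the end-point only, so improvement from baseline cannot be computed for them. This stands, and the fix below is confined to end-point values.

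**Conclusion.** The point holds at practice level on the documents' own text. FEV1 is not scheduled in randomised practices that do not participate, participation is expected to depend on strategy, and a between-strategy FEV1 comparison is therefore conditional on a post-randomisation event. It cannot carry the intention-to-treat label. That unwilling patients inside participating practices also lack FEV1 is probable but unstated.

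The size of the selection is unknown. The 0.08 to 0.27 SD above rests wholly on assumed participation fractions and correlations.

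Two related facts are documented. MS patients are evaluated only at six months in the text but at 0, 3 and 6 months for FEV1 in Table 4. And FEV1 is not alone: MARS and B-IPQ also lack N. They are coded for IS and ES only, so they offer no comparison with MS either.

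This should be corrected, but it does not threaten the primary analyses.

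**What to change.** 1. Reconcile Table 4 and its legend with Study design, Endpoint evaluation and the spirometer text under Table 4. State who has FEV1 measured, at which times and in which strategies, and add a code for unwilling patients in participating practices.
2. In the Analysis section, exclude FEV1 from the intention-to-treat comparisons between strategies. Report it descriptively among measured participants, with change only where a baseline exists, and claim no causal strategy effect.
3. Apply the same label to MARS and B-IPQ.
4. Base the between-strategy clinical comparison on end-point values of outcomes scheduled for both all strategies and N. In Table 4 as printed these are AQLQ and EQ-5D; heiQ and the cost questionnaire carry N but no entry for MS. An N entry makes such a comparison possible. It does not guarantee that the data will be complete.

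The cost is a few sentences and table codes, with no new data. The downside is that the trial gives up a between-strategy claim on lung function, which the present schedule cannot support.

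### The emergency-care and hospital-admission part of the exacerbation outcome is collected on a different schedule in the minimum strategy (MS), so the comparison between strategies may be biased

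*Protocol article*

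**What the plan says.** The abstract lists the presence of exacerbations as a secondary effect measure. The Analysis section compares differences between strategies by intention to treat.

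The Patient level section (text under Table 4) gives three routes to an exacerbation:

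- "deterioration in asthma that required emergency treatment or hospitalization (collected by quarterly questionnaire");
- "the need for oral steroids for three days or more (collected by pharmacy records");
- "the need for oral steroids for asthma as judged by the attending physician".

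It then defines moderate exacerbations by features "lasting for two or more days: deterioration in symptoms, deterioration in lung function, and/or increased rescue bronchodilator use", and names no data source for them.

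On timing, the Study design section says: "In the ES and IS strategies, individual patient outcomes will be evaluated at baseline", and again at three and six months. For the minimum strategy it says: "Individual patient outcomes in the MS strategy will be evaluated at six months (end-point evaluation"). The Endpoint evaluation section confirms that MS patients, and IS/ES patients unwilling to use the programme, have only the six-month contact.

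Table 4 has no row for exacerbations. The cost questionnaire is marked for IS and ES at 0, 3 and 6 months and for non-participating practices at 6 months. MS participants are not marked for it at any visit. The Cost-effectiveness section calls this questionnaire quarterly.

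**The concern.** A questionnaire cannot be quarterly for patients who are approached once. The same event is therefore sought repeatedly, with short recall, in IS/ES participants, and once, with recall of up to six months or over an unstated shorter period, in every MS patient. This difference follows the randomised arm, so randomisation does not remove it.

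The likely direction is under-counting in MS. That would make the supported strategies look worse on exacerbations than they are, or hide a real reduction. A larger sample would not correct it.

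**Working it through.** **Schedule by group (emergency-care and hospital component)**

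| Group | Contacts in the text | Cost questionnaire in Table 4 |
|---|---|---|
| IS/ES participants | 0, 3, 6 months | 0, 3, 6 months |
| IS/ES decliners | 6 months | not marked separately |
| MS patients | 6 months | none |

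The exacerbation definition does not name its questionnaire. That it is the cost questionnaire is an inference from the word quarterly. The text alone already gives MS a single contact.

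Table 4 does not settle the MS schedule. It marks quality of life and lung function for all strategies at 0, 3 and 6 months, which conflicts with the Study design and Endpoint evaluation sections. Neither measure records emergency or hospital care.

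**What limits the bias.** The pharmacy-record and physician-judgement routes are not described as differing by arm. Only events that no other route would show are exposed.

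**Illustration.** The article gives no exacerbation rate and no capture probability, so these are assumptions:

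- p = true six-month risk, equal in all arms (10% to 30%);
- q = share of events seen only by the unequal route;
- s = fraction of those events captured in MS, with full capture in IS/ES.

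Observed MS risk: m = p[(1 − q) + q·s]. Spurious difference: d = p·q·(1 − s).

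The Sample size calculation section supplies 14 practices × 10 patients = 140 per arm and an intra-cluster correlation of 0.25, hence a design effect of 1 + 9 × 0.25 = 3.25. The 140 reproduces for 5% against 30%, two-sided 0.05, 80% power, with continuity correction: 43 × 3.25 = 139.75. That correlation was set for participation; using it for exacerbations is a further assumption.

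SE = √{3.25 × [p(1 − p) + m(1 − m)]/140}; rejection probability = Φ(d/SE − 1.96) + Φ(−d/SE − 1.96).

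Example: p = 0.20, q = 0.5, s = 0.5 gives m = 0.15, d = 0.05, SE = √(3.25 × 0.2875/140) = 0.0817, and a rejection probability of 9.4% instead of 5%.

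| q | s | d in points, p = 10 / 20 / 30% | Rejection probability |
|---|---|---|---|
| any | 1 | 0 | 5% |
| 0.25 | 0.5 | 1.25 / 2.5 / 3.75 | 5.5 / 6.0 / 6.7% |
| 0.5 | 0.75 | 1.25 / 2.5 / 3.75 | 5.5 / 6.0 / 6.7% |
| 0.5 | 0.5 | 2.5 / 5 / 7.5 | 7.0 / 9.4 / 12.5% |
| 1 | 0.5 | 5 / 10 / 15 | 14.3 / 25.9 / 39.5% |

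Only q(1 − s) matters. The last row therefore also describes q = 0.5 with s = 0, which is the case if the cost questionnaire is the source and MS patients never receive it.

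**Dilution by decliners.** If only a share f of IS/ES patients has repeated contact and the rest are captured as in MS, then d = p·q·f·(1 − s). Take f = 0.30 purely as an example, borrowing the planning figure for frequent use (5% plus 25 points). With s = 0.5, IS/ES capture of the exposed events is 0.30 + 0.70 × 0.5 = 0.65 against 0.50 in MS, a ratio of 1.3. The fourth row of the table (q = s = 0.5) then shrinks to between 0.3 × 2.5 = 0.75 and 0.3 × 7.5 = 2.25 points.

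**The case against.** The strongest reply is that only part of one secondary outcome is affected. An emergency episode that led to oral steroids may also be found through pharmacy records or the physician. A six-month questionnaire could ask about the whole period. IS/ES decliners are also contacted once. The Discussion says research activity in MS was kept low on purpose, because it could itself stimulate uptake. All of this stands. It limits the size and makes the bias possible rather than certain, but it does not make ascertainment equal.

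A reader might infer more than the article supports:

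- *A two-fold excess in IS/ES (6/3 = 2.0).* This needs a month-6 questionnaire that looks back only three months, which is not stated, and it ignores the decliners and the oral-steroid routes. With complete six-month recall the ratio is 1.0.
- *A six-fold excess of moderate events (0.30/0.05).* This is a ratio of two planning rates for programme use. It needs self-monitoring to be the only source, with complete detection in frequent users and none in anyone else. The article never names self-monitoring as a source, and PatientCoach is offered in every strategy. A condensed article may also leave the source of a sub-definition to the full protocol.
- *That this is the trial's main harm outcome.* The article lists it as one of four secondary clinical effect measures.

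**Conclusion.** The concern holds for the emergency-care and hospital component. As written, the plan collects it at a different frequency and over a different recall period by strategy, and the between-strategy comparison may be biased, probably by under-counting in MS. The document does not allow the size to be computed. On the stated assumptions it runs from zero (complete six-month recall, or every event visible by another route) to 15 points in the extreme case of 30% risk and half of all events missed in MS. Middle assumptions give 2.5 to 7.5 points, and less when many IS/ES patients decline. Because the outcome is secondary and part of it is records-based, this should be corrected but does not threaten the trial's primary conclusions.

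**What to change.** For the between-strategy comparison, count exacerbations in all three arms, participants and decliners alike, from the same sources over the same fixed six months:

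- Use the pharmacy records named in the definition and the practice records that the Economic evaluation section already plans, where medical costs are "assessed from electronic patient records (with written patient permission").
- If a patient report is kept, ask everyone one emergency-care and admission item at the month-6 endpoint, with six-month recall.
- Treat month-3 questionnaire data in IS/ES as supplementary.
- Do not compare moderate exacerbations between strategies unless they have a source common to all arms.
- Reconcile Table 4 with the Study design and Endpoint evaluation sections on the MS schedule.

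The cost is small, and no MS contact before the endpoint is added, so the low research burden in that arm is kept. Permission for record access must be sought from MS patients and decliners, and may be incomplete. The article mentions the records for costs such as prescribed medication, so emergency and hospital fields may need adding to the extraction. Events that reach neither the records nor the endpoint recall are lost. Recording could still differ somewhat between supported and unsupported practices, so the change reduces the bias but may not remove it.
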